### 2.7. Blinding

Because it is not possible to blind the participants due to the nature of group assignment, we designed the trial to blind the outcome assessor to minimize the related bias. The effect evaluation of the participants will be conducted by an investigator who will not prescribe the investigational product and will not have access to any source documents, including medical records and case report form (CRF). The outcome assessor only asks questions related to the evaluation items and does not know which group the clinical trial participants are assigned to.

### 2.8. Interventions

Participants will be randomly assigned to receive YGJ, PWS, or usual care for 6 weeks. All investigational drugs in the YGJ and PWS groups were manufactured by Kracie Pharma Korea Co., Ltd. (Seoul, Republic of Korea) and Hanpoong Pharm & Foods Co., Ltd. (Jeonju, Republic of Korea), respectively, in compliance with the Korean Good Manufacturing Practice guidelines.

YGJ (Kracie Yukgunja-tang Extract Fine Granule; product code: 201310401) is a light-brown-to-brown-colored fine granule, and participants will consume one pack (3.0 g) twice a day before or between meals for 6 weeks. The raw materials of YGJ extract per pack are Ginseng Radix 2 g; Atractylodis Rhizoma Alba 2 g; Poria Sclerotium 2 g; Pinelliae Tuber 2 g; Citri Unshius Pericarpium 1 g; Zizyphi Fructus 1 g; Zingiberis Rhizoma Recens 0.25 g; and Glycyrrhizae Radix et Rhizoma 0.5 g. PWS (Hanpoong Pyeongwi-san, mixed single extract; product code: 200000079), an active control, is a brown-colored powder, and participants will consume one pack (2.18 g) three times a day before or between meals for 6 weeks. The component per 1 pack is a powder extract of Atractylodis Rhizoma 0.95 g; Citri Unshius Pericarpium 0.56 g; Magnoliae Cortex 0.10 g; Glycyrrhizae Radix et Rhizoma 0.20 g; Zingiberis Rhizoma Recens 0.03 g; and Zizyphi Fructus 0.34 g. All investigational products will be stored at room temperature, and a pharmacist will check their storage, dispensation, and quality. During the administration of the investigational products, investigators will check the number of remaining drugs to ensure that the participants have taken the drugs properly (Visits 3 and 4). Medication compliance (%) will be calculated by dividing the number of drugs actually taken by the number of drugs that should have been taken.

During the clinical trial period, dietary guidelines based on dietary recommendations prepared for Korean dyspepsia patients [20] will be distributed and explained to all participants in the three groups. The usual care group will perform daily management while following the dietary guidelines distributed during the clinical trial period without administration of any investigational product. Under the judgement of the investigator, medications and treatments other than those prohibited in this clinical trial may be permitted, and all medications and treatments performed during the trial period should be recorded in the CRF. YGJ and PWS groups are also allowed to perform usual care.

Concomitant medications are permitted only if the investigators determine that they do not affect the outcomes of this study, including drugs used to treat underlying diseases or therapeutic drugs in case of adverse events. The investigators will check and record all the detailed information of concomitant medications in the CRF. During the entire trial period, participants are prohibited from taking medications, including proton pump inhibitors, histamine receptor antagonists, antacids, prokinetics, antidepressants, gastric fundus relaxants, gastric mucosal protectants, nonsteroidal anti-inflammatory drugs, anticholinergics, oral corticosteroids, and treatment regimens for *Helicobacter pylori*, which, in the opinion of the investigators, may affect the gastrointestinal tract. In addition, it is prohibited to receive Korean medicine treatments such as acupuncture, herbal medicine, or moxibustion for the purpose of improving indigestion during the clinical trial period.

### 2.9. Outcome Measures

#### 2.9.1. Demographic and Baseline Information

Demographic information, including date of birth, age, sex, history of smoking, drinking, caffeine consumption, and exercise habits, will be investigated and recorded in the CRF. Socioeconomic characteristics such as educational background, conjugality, occupation, religion, and household income will also be collected for economic analysis. The morbidity period of FD and recent upper endoscopy findings will be investigated, and the subtypes of FD—epigastric pain syndrome (EPS), postprandial distress syndrome (PDS), and the overlap of the two subgroups—will be determined according to Rome IV. PDS is a condition in which there is a feeling of fullness after a meal or bothersome early satiety, whereas EPS is characterized by unpleasant epigastric pain or burning, not necessarily related to food intake. The clinically significant medical history and surgery history within the last 1 year and treatment history within the last 4 weeks of the participants will be investigated and recorded in the CRF.

In addition, deficiency and excess pattern identification will be evaluated and recorded under the judgment of a Korean medicine doctor. Investigators will perform a systemic physical examination; collect baseline characteristics, including height, weight, and body mass index; and check for infection of *Helicobacter pylori* using Anti-*Helicobacter pylori* IgG serology at the screening visit. Furthermore, the participants will assess their health status related to FD for the past two weeks using a standard tool for pattern identification of FD [21] Then, they will be classified into the following six pattern identifications: spleen–stomach deficiency and cold, spleen deficiency with qi stagnation, liver–stomach disharmony, cold–heat complex, spleen–stomach dampness and heat, and dietary retention and stagnation.

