### 2.4. Exclusion Criteria

Diagnosed with specific diseases, including peptic ulcer, esophageal cancer, MALT lymph cancer, stomach cancer, colon cancer, biliary tract and pancreatic diseases (except asymptomatic cholelithiasis), and inflammatory bowel disease within 1 year prior to the screening visit;Having more severe symptoms of reflux esophagitis and irritable bowel syndrome than those of dyspepsia (Participants with reflux esophagitis or irritable bowel syndrome can participate in this clinical trial. However, through the participants’ interview and medical history taking, participants whose symptoms of reflux esophagitis (including reflux and heartburn) and irritable bowel syndrome (including abdominal pain or discomfort related to the pattern of defecation) are more severe than those of dyspepsia are excluded.);Having alarming symptoms such as severe weight loss, bloody stool, dysphagia, swallowing pain, and persistent vomiting;Diagnosed with mental disorders, such as major depressive disorder, anxiety disorder, and panic disorder, or having a depression score of 11 or higher on the Hospital Anxiety and Depression Scale (HADS) at the screening visit;Having serious systemic diseases in heart, lung, liver, or kidney, or presence of other malignant diseases;Having a history of gastrointestinal surgery (except for appendectomy more than 6 months ago);Taking medications that can affect the gastrointestinal tract, including proton pump inhibitors, histamine receptor antagonists, antacids, prokinetics, antidepressants, gastric fundus relaxants, gastric mucosal protectants, nonsteroidal anti-inflammatory drugs, anticholinergics, or oral corticosteroids, or receiving *Helicobacter pylori* eradication treatment, within 2 weeks prior to the screening visit (taking low-dose aspirin (100 mg/day or less) for the purpose of preventing cardiovascular disease is allowed);Having received Korean medicine treatments such as acupuncture, herbal medicine, or moxibustion for the purpose of improving dyspeptic symptoms within 2 weeks prior to the screening visit, or who are planning to receive them during the trial period;Having severe liver or renal diseases (aspartate aminotransferase or alanine aminotransferase levels ≥ 3 times the upper limit of normal levels or creatinine levels ≥ 2 times the upper limit of normal levels);Having a history of alcohol or drug abuse;Women who are pregnant or lactating, or women who do not agree to use effective methods of contraception during the clinical trial;Having genetic problems, such as galactose intolerance, Lapp lactase deficiency, or glucose-galactose malabsorption;Having known hypersensitivity to investigational products (according to the Korean Ministry of Food and Drug Safety (KMFDS), adverse events such as pseudoaldosteronism, myopathy, and skin reactions (rash, redness, itching, hives) may occur after the administration of YGJ and PWS.);Having taken other investigational products within 3 months; andHaving judged to be unsuitable for participation in this trial by investigators.

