**Hypothesis** **3.**
*[*

$H_{0}\;:\;\mu_{3}-\mu_{1}>M,\;H_{1}\;:\;\mu_{3}-\mu_{1}\;\leq M$

*]*

*-*

$\mu_{1}$

*: Change in TDS score of the YGJ group at week 6*

*-*

$\mu_{3}$

*: Change in TDS score of the PWS group at week 6*

To evaluate the noninferiority of YGJ compared to PWS, Hypothesis 3 will be tested in the same way as Hypothesis 1. However, since the noninferiority test is a single test, the significance level will be set to 2.5%, and the noninferiority margin will be defined as the lower limit of the 95% CI of Hypothesis 2. The multiple test problem will be solved using the fixed sequence method [29]. In other words, if the statistical test result for Hypothesis 1 is significant, the test for Hypothesis 2 will be performed, and if the statistical test result for Hypothesis 1 is not significant, the test for Hypothesis 2 and Hypothesis 3 will not be performed. If the statistical test result for Hypothesis 1 is significant and the test for Hypothesis 2 is performed, and if the statistical test result for Hypothesis 2 is significant, the test for Hypothesis 3 will be performed. If the statistical test result is not significant, the test for Hypothesis 3 will not be performed. If possible, subgroup analysis will be performed by categorizing the participants’ baseline characteristics, including age (65 years old or older/under), Rome IV subtype (EPS, PDS, and overlap), type of FD pattern identification (according to the standard tool for pattern identification of FD [21]: spleen–stomach deficiency and cold, spleen deficiency with qi stagnation, liver–stomach disharmony, cold–heat complex, spleen–stomach dampness and heat, and dietary retention and stagnation), deficiency and excess pattern identification, and the presence or absence of *Helicobacter pylori* infection and spleen qi deficiency syndrome (cut off score: 43.18 points in SQDQ [27]). In addition, we will combine the results of the YGJ and PWS groups corresponding to herbal medicine and compare them with the usual care control group.

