## Figures and Tables

**Figure 1 healthcare-11-01456-f001:**
[figure not shown]
Flow chart of the trial process.

**Table 1 healthcare-11-01456-t001:** Schedule of enrolment, interventions, and assessments.

	Study Period					
	Enrolment	Allocation	Medication		Follow-Up	
Procedures	Visit 1 (Screening)	Visit 2	Visit 3	Visit 4	Visit 5	Visit 6 (Telephone)
TIMEPOINT	−2 weeks	Week 0	Week 3 ±4 days	Week 6 ±4 days	Week 9 ±4 days	Week 24 ±4 days
ENROLLMENT						
Eligibility screen	●					
Informed consent	●					
Demographics	●					
Medical and treatment history	●					
Physical examination	●					
Vital signs	●	●	●	●	●	
PIFD	●					
Allocation		●				
INTERVENTIONS						
YGJ or PWS		○	○	○		
Dietary guideline education		●	●	●		
ASSESSMENTS						
TDS		●	●	●	●	●
SDS		●	●	●	●	
OTE			●	●	●	●
VAS (dyspepsia)	●		●	●	●	
FD-QoL		●	●	●		
HADS	●		●	●	●	
EQ-5D-5L EQ-VAS		●	●	●	●	●
SQDQ		●	●	●		
DQ		●	●	●		
Cost questionnaire		●	●	●	●	●
Laboratory tests *	●			●		
Adverse events investigation		●	●	●	●	
Compliance test			○	○		

●: all participants, ○: YGJ and PWS groups, * Including hematological, blood glucose level, liver and renal function tests, electrolyte test, acyl-ghrelin, and deacyl-ghrelin. In addition, human chorionic gonadotropin urine test for women in their childbearing years, and anti-*Helicobacter pylori* serum IgG testing at the screening visit. Abbreviations. DQ, Damum questionnaire; EQ-VAS, the EuroQol visual analog scale; EQ-5D-5L, five-level version of the EuroQol five-dimensional descriptive system; FD-QoL, functional dyspepsia-related quality of life; HADS, hospital anxiety and depression scale; OTE, overall treatment effect; PIFD, pattern identification of functional dyspepsia; PWS, Pyeongwi-san; SDS, single dyspepsia symptom; SQDQ, spleen qi deficiency questionnaire; TDS, total dyspepsia symptom; VAS, visual analog scale; YGJ, Yukgunja-tang.

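### The planned subgroup by H. pylori infection rests on screening IgG serology alone, so previously eradicated participants who are still seropositive would be counted as infected

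*Protocol article*

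**What the plan says.** Four statements in the protocol article bear on this point.

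- **Test.** Section 2.9.1 has investigators check for infection with "Helicobacter pylori* using Anti-*Helicobacter pylori* IgG serology at the screening visit". The footnote to Table 1 lists the same assay, "anti-*Helicobacter pylori* serum IgG testing at the screening visit". No test of active infection is named anywhere.
- **Entry.** Section 2.4 excludes people "receiving *Helicobacter pylori* eradication treatment, within 2 weeks prior to the screening visit". Eradication before that window is not an exclusion. Section 2.8 prohibits H. pylori regimens during the trial, so only eradication before entry matters here.
- **History.** Section 2.9.1 states that "treatment history within the last 4 weeks of the participants will be investigated and recorded in the CRF". Clinically significant medical and surgical history goes back 1 year, and recent upper endoscopy findings are also recorded. No item on past eradication is named.
- **Use.** Section 2.11, in the text after Hypothesis 3, says "If possible, subgroup analysis will be performed by categorizing the participants’ baseline characteristics". One of the listed factors is "the presence or absence of *Helicobacter pylori* infection and spleen qi deficiency syndrome". Section 2.12 says the economic subgroup analysis follows the same plan.

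**The concern.** The subgroup factor is named as infection, but the variable behind it is an antibody result. IgG records that a person has met the organism; it does not separate a current infection from one that has been cured. The entry rule allows people with past eradication to enrol, so the seropositive stratum can hold both kinds of participant.

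At stake is the reading of the subgroup result. If cured participants respond like uninfected ones, mixing them into the infected stratum pulls the two strata together. A real difference in treatment effect by infection status would look smaller than it is, and a small or null difference would be reported under a label that the data do not support. The economic subgroup analysis would carry the same label.

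**Working it through.** The plan states no figure on this point, so there is none to reproduce. The check sets the sections side by side and then sizes the dilution on declared assumptions.

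**Step 1: who can be mislabelled.** Take a participant whose eradication treatment succeeded and ended, say, two years before screening.
- Section 2.4: eligible on this criterion, since the window is 2 weeks.
- Section 2.9.1: the treatment lies outside both the 4-week and the 1-year windows.
- Screening IgG: if still positive, the participant is classed as infected under sections 2.9.1 and 2.11. If it has turned negative, the participant is classed as uninfected, which is correct.

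The mislabelled group is therefore the cured participants who are still seropositive, not all cured participants.

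**Step 2: their share of the infected stratum.** Let c be the cured share of ever-infected participants and p the chance that IgG is still positive after cure. Take every currently infected participant as IgG-positive. Then

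e = c·p / (c·p + 1 − c)

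The documents give neither c nor p. On assumed values:

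| c | p | e |
|---|---|---|
| any of 0.1 to 0.6 | 0 | 0 |
| 0.1 | 0.25 | 0.025 / 0.925 = 0.03 |
| 0.2 | 0.5 | 0.10 / 0.90 = 0.11 |
| 0.4 | 0.75 | 0.30 / 0.90 = 0.33 |
| 0.6 | 1.0 | 0.60 / 1.00 = 0.60 |

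**Step 3: effect on the contrast.** Let D be the true difference in treatment effect between infected and uninfected participants. If cured participants respond like uninfected ones and seronegatives are uninfected, the observed difference is (1 − e)·D. The sample size needed to detect it rises by 1/(1 − e)².

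**Step 4: what the fix recovers.** Removing the mislabelled participants restores D but shrinks the seropositive stratum to (1 − e) of its size. With equal strata, the variance goes from 1 + 1 = 2 units to 1 + 1/(1 − e). The net gain is the figure from step 3 divided by that variance ratio.

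| e (assumed) | Contrast retained, 1 − e | 1/(1 − e)² | Variance ratio after removal | Net gain |
|---|---|---|---|---|
| 0.10 | 0.90 | 1.23 | 2.11/2 = 1.06 | 1.17 |
| 0.20 | 0.80 | 1.56 | 2.25/2 = 1.13 | 1.39 |
| 0.40 | 0.60 | 2.78 | 2.67/2 = 1.33 | 2.08 |

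The last column, not the third, is the fair measure of what is gained. It still assumes that exactly the cured seropositives are removed. An eradication-history question would also remove people whose treatment failed, and previously treated people who are now seronegative, so the real gain would be somewhat less.

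**The case against.** The best case against acting has four parts.

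1. **Persistence of IgG after cure is not in the documents.** With p = 0 there is no dilution. It stands that the size is unknown and that a flat claim that all cured participants are put in the infected stratum would be wrong. It does not remove the mismatch: that an antibody test shows exposure rather than current infection is a general property of the test.
2. **The case report form is not shown.** A reader might infer that the collected history cannot correct the label at all. The documents do not support that. The 1-year history or the endoscopy findings may reveal some eradications, investigators must ask about recent eradication to apply section 2.4, and the full form may hold more. But no section links any of these to the subgroup, and treatment more than a year earlier falls outside the stated windows.
3. **The subgroup is peripheral.** This stands. It is conditional and one of several factors, and it lies outside Hypotheses 1 to 3, the fixed sequence and the sample size. Randomisation is not stratified (section 2.6). With 28 participants planned in usual care, a contrast by serostatus would be imprecise with any test.
4. **Asking about past eradication does not measure current infection.** This also stands. A seropositive, never-treated participant is not proven to be infected. The fix reduces misclassification and corrects the label, and it should claim no more than that.

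**Conclusion.** The concern holds in a limited form. The article defines a subgroup by infection, names only a marker of exposure to fill it, and admits people with eradication more than 2 weeks before screening. Followed as written, the plan counts previously eradicated participants who remain seropositive as infected.

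Any infection contrast is then multiplied by 1 − e, provided cured participants respond like uninfected ones and seronegatives are uninfected. The value of e is unknown; 10% to 40% is an assumption, and values near zero are possible if few entrants were treated or if IgG fades soon after cure.

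A reader might infer a 1.2- to 2.8-fold loss of information that the fix would win back. That overstates it: once the participants dropped from the contrast are counted, the net gain over the same range is about 1.2 to 2.1 fold, and then only with equal strata. A reader might also infer that the trial's main conclusions are at risk. They are not: the primary analysis, the sample size and the tests of Hypotheses 1 to 3 do not use this variable.

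**What to change.** - In sections 2.9.1 and 2.11, name the variable H. pylori serostatus instead of infection.
- At Visit 1, record whether the participant ever had eradication treatment (yes, no, unknown) and whether cure was confirmed.
- Base the subgroup contrast on seronegative versus seropositive-never-treated participants. Show previously treated participants separately, and say in advance where the unknowns go.
- State that current infection is not measured.
- Apply the same definition to the economic subgroup analysis in section 2.12.

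**Cost.** One case report form item and a changed subgroup definition, with no extra test and no change to eligibility or treatment. The downsides are a small third category, some recall error about past treatment, and slightly fewer participants in the contrast. If enrolment is too far advanced to add the item, the relabelling and the statement about current infection can still be made at no cost.

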#### 2.9.2. Primary Outcome: Total Dyspepsia Symptom Scale (TDS)

The TDS questionnaire evaluates eight items consisting of postprandial fullness/bloating, early satiety, epigastric pain and burning, nausea, vomiting, belching, and other dyspeptic symptoms on a 4-point Likert scale (0: none, 1: mild/weak, 2: moderate/average, and 3: severe) [11]. A higher overall score, obtained by adding up the points for each item, indicates more severe symptoms related to indigestion. The TDS has been used as a primary outcome in a number of clinical trials related to FD [11,19,22]. Therefore, the TDS will be measured at all visits except the screening visit. The degree of improvement in the TDS score during the trial period will be calculated using the following formula: $$\mathrm{Improvement}\;\mathrm{in}\;\mathrm{TDS}\;\left(\%\right)=\frac{TDS\;at\;baseline-TDS\;at\;N\;th\;week}{TDS\;at\;baseline}\times 100$$

The therapeutic effects will be classified as significant (≥75%), moderate (≥50%), mild (≥25%), and none (<25%) according to the improvement rate.

#### 2.9.3. Secondary Outcomes

(1) Single Dyspepsia Symptom Scale (SDS)

The SDS questionnaire evaluates the frequency, intensity, and bothersomeness of the most common symptoms of FD, using a 4-point Likert scale, i.e., by measuring the following symptoms: postprandial fullness/bloating, early satiety, and epigastric pain and burning [11]. A higher sum of scores corresponding to the symptoms means more severe indigestion. SDS will be obtained at all visits except the screening visit and telephone follow-up (Visit 6). The degree of improvement in the SDS score will be calculated in the same way as that of the TDS.

(2) Overall Treatment Effect (OTE)

Using the OTE questionnaire, the subjectively perceived therapeutic effect on dyspeptic symptoms and quality of life will be assessed. At all visits after allocation, participants will be asked about how much their symptoms improved compared to before participating in the clinical trial, by answering with one of the following 7 items: “very much worse,” “much worse,” “slightly worse,” “no change,” “slightly improved,” “much improved,” and “very much improved” [12]. The response rate for each item will be calculated, and participants who responded “much improved” or “very much improved” will be defined as responders.

(3) VAS for Dyspepsia

Participants will check the intensity of dyspepsia symptoms over the past 2 weeks themselves using a VAS in a horizontal line drawn from 0 (not uncomfortable at all) to 100 (the worst dyspepsia you can imagine). The scores will be obtained at all visits except baseline (Visit 2) and telephone follow-up (Visit 6).

(4) FD-related Quality of Life (FD-QoL)

The FD-QoL is a questionnaire used to evaluate the quality of life of patients with FD, which consists of 21 items in four dimensions, including psychological, role-functioning, eating, and liveliness status. It has been validated for Korean patients with FD, where lower scores represent a worse quality of life [23]. Data will be collected at baseline (Visit 2), week 3 (Visit 3), and week 6 (Visit 4).

(5) HADS

The HADS questionnaire has a total of 14 items and consists of seven anxiety subscales and seven depression subscales. Each item is evaluated on a 4-point scale, and a higher score means more complaints of symptoms [24]. It will be measured at all visits except baseline (Visit 2) and telephone follow-up (Visit 6).

(6) Five-level Version of the EuroQol Five-dimensional Descriptive System (EQ-5D-5L)

The EQ-5D-5L is a self-reporting questionnaire applied to evaluate quality of life. It comprises five dimensions as follows: mobility, self-care, usual activities, pain/discomfort, and anxiety/depression [25]. In addition, participants’ self-rated health status will be recorded on a vertical VAS scale drawn from 0 (the worst health you can imagine) to 100 (the best health you can imagine). It will be assessed at all visits except the screening visit.

(7) Spleen Qi Deficiency Questionnaire (SQDQ)

The SQDQ consists of 11 items associated with symptoms such as loss of appetite, reduced food intake, and general fatigue, evaluated on a 5-point scale [26]. After applying weight conversion to each question, if the total score exceeds 43.18 points, the participants will be diagnosed as spleen qi deficiency [27]. Data will be collected at baseline (Visit 2), week 3 (Visit 3), and week 6 (Visit 4).

(8) Damum Questionnaire (DQ)

The DQ is an instrument for determining if a participant has symptoms of phlegm pattern such as dizziness, chest discomfort, and indigestion. It includes a total of 14 items on the basis of a 7-point scale. Higher scores calculated by multiplying the weights indicate a high possibility of the existence of Damum [28]. The DQ will be evaluated at baseline (Visit 2), week 3 (Visit 3), and week 6 (Visit 4).

(9) Serum Ghrelin Levels

We will evaluate serum levels of acyl-ghrelin and deacyl-ghrelin, and the ratio of acyl-ghrelin to total ghrelin by collecting serum acyl-ghrelin and deacyl-ghrelin at the screening visit and week 6 (Visit 4).

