### 2.3. Inclusion Criteria

Adults aged 19–75 years at the time of screening visit;Diagnosed with FD according to Rome IV criteria (having one or more symptoms of postprandial fullness, early satiety, epigastric pain, and epigastric burning without organic findings, occurred at least 6 months ago and persisted for at least past 3 months);The intensity of dyspeptic symptoms measured by a 0–100 mm visual analog scale (VAS) is at least 40 points; andVoluntarily signed written informed consent approved by the institutional review board (IRB).

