Other secondary outcome measures will be tested in the same way as the primary outcome measure. In addition, to compare the difference between the values before and after treatment in each group, the continuous variable will be analyzed using Student’s paired *t*-test or Wilcoxon signed-rank test, and the discrete variable will be Fisher’s exact test. Repeated measures analysis of variance will be performed to compare the differences in trend change in each group of visits, and Dunnett’s procedure (based on the baseline) will be used as a multiple comparison correction.

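### The dyspepsia VAS has no Visit 2 value, so its within-group before/after tests start from the screening score that decided entry and will count regression to the mean as improvement

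*Protocol article*

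**What the plan says.** Section 2.9.3 sets the VAS schedule: "The scores will be obtained at all visits except baseline (Visit 2) and telephone follow-up (Visit 6". For HADS it says: "It will be measured at all visits except baseline (Visit 2) and telephone follow-up (Visit 6". Table 1 agrees. Both are taken at screening and at weeks 3, 6 and 9, and neither is taken at week 0.

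Both scales also decide eligibility. Section 2.3 requires that "The intensity of dyspeptic symptoms measured by a 0–100 mm visual analog scale (VAS) is at least 40 points". Section 2.4 excludes anyone "having a depression score of 11 or higher on the Hospital Anxiety and Depression Scale (HADS) at the screening visit". There is no cut-off on the anxiety subscale. Table 1 places the eligibility screen and the only pre-allocation VAS at Visit 1, so the qualifying VAS is the screening VAS.

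Section 2.1 places a 2-week run-in between screening and allocation. The VAS looks backwards: "Participants will check the intensity of dyspepsia symptoms over the past 2 weeks themselves using a VAS". The screening VAS therefore describes a period that ends before the run-in begins.

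For secondary outcomes, section 2.11 first applies the between-group method of the primary outcome. It then adds paired t-tests or Wilcoxon signed-rank tests "to compare the difference between the values before and after treatment in each group", and a repeated-measures analysis with Dunnett comparisons against baseline. TDS, SDS, FD-QoL, EQ-5D-5L, SQDQ and DQ all have a Visit 2 value.

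**The concern.** When people are admitted because a fluctuating score was high on one day, their next score is lower on average even if nothing has changed. A paired test that starts from the qualifying score takes in that fall. Here no later pre-treatment VAS exists to start from, so the fall is built into every within-group VAS test. Any change during the run-in is added to it, because the screening VAS covers only the time before.

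At stake is how the within-group VAS results will be read. A significant fall could appear in each arm, usual care included, without any effect of treatment. The herbal arms are twice the size of the usual care arm, so the same artefact reaches significance more often in them. A result that is significant within the herbal arms but not within usual care could then arise with no drug effect at all.

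**Working it through.** **The plan's own figures.** The protocol gives no number for the VAS baseline or for regression to the mean. It does supply the group sizes. Section 2.10 assumes a TDS difference of 2.70, SD 3.65, alpha 0.05, 80% power and a 2:1 ratio. For usual care, n = (1.960 + 0.842)² × (1 + 1/2) × 3.65² / 2.70² = 7.85 × 1.5 × 1.83 = 21.5, so 22, with 44 for YGJ, as stated. With 20% dropout the plan randomises 56, 56 and 28. I use 56 and 28 as randomised numbers and 44 and 22 as evaluable numbers.

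**Assumed inputs (not in the documents).** Unselected VAS mean 45 to 55, SD 15 to 20, retest correlation r 0.5 to 0.8. Scores are treated as bivariate normal with no true change over time.

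**Formulas.** Let a = (40 − mean)/SD and λ = φ(a)/(1 − Φ(a)). Selected participants average mean + SD·λ at screening and mean + r·SD·λ later. The expected fall is therefore (1 − r)·SD·λ. The variance of the change is (1 − r)²·SD²·[1 − λ(λ − a)] + (1 − r²)·SD². The chance of a significant fall follows from the noncentral t distribution.

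**Worked case: mean 50, SD 20, r = 0.6.**
- a = −0.5; λ = 0.3521/0.6915 = 0.509.
- Fall = 0.4 × 20 × 0.509 = 4.1 mm.
- Variance of change = 0.16 × 400 × [1 − 0.509 × 1.009] + 0.64 × 400 = 31 + 256 = 287, so the SD of change is 16.9.
- n = 56: noncentrality 4.07/(16.94/√56) = 1.80.
- n = 28: noncentrality 4.07/(16.94/√28) = 1.27.

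**Chance of a significant fall with no true change** (two-sided 5% test, so nominally 2.5% in this direction):

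| Mean, SD, r | Fall (mm) | n = 56 | n = 28 | n = 44 | n = 22 |
|---|---|---|---|---|---|
| 50, 20, 0.6 | 4.1 | 42% | 23% | 34% | 19% |
| 50, 17.5, 0.65 (middle of the ranges) | 2.9 | 33% | 18% | 27% | 15% |
| 45, 20, 0.5 (largest fall) | 6.5 | 73% | 43% | 62% | 35% |
| 55, 15, 0.8 (smallest fall) | 0.9 | 10% | 7% | 9% | 6% |

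Simulation of the truncated scores agrees with these rates to within about one percentage point. If the unselected mean were 60 (SD 15, r = 0.7), the fall would be 0.8 mm and the rate at n = 56 about 8%.

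**HADS depression.** Here the cut-off keeps low scores. With b = (10.5 − mean)/SD, the expected shift is a rise of (1 − r)·SD·φ(b)/Φ(b). With an assumed unselected mean of 5 to 9, SD 3 to 4 and r 0.5 to 0.8, it runs from 0.05 points (5, 3, 0.8) to 1.15 points (9, 4, 0.5).

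**The case against.** The strongest reply is that these tests are supplementary. Secondary outcomes are first compared between groups by the primary method, and the trial's hypotheses are all between arms. The protocol nowhere says that a within-group change will be read as a treatment effect. Strictly, a paired test asks only whether the group mean changed, and after selection it does change. This is fair, and it limits the importance of the point. It does not remove it: a before/after test around a treatment period invites the reading that treatment caused the change, and the schedule makes the VAS version wrong by construction.

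A reader might infer that HADS is inflated in the same way. The documents do not support that. Excluding depression scores of 11 or higher selects low scores, so regression pushes depression up and can hide improvement or look like worsening. Anxiety is not selected on and has only an older baseline. A reader might also infer that the efficacy comparisons are biased. They are not: all arms pass the same cut-offs before randomisation, and TDS has its own Visit 2 baseline.

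It is also true that the size rests wholly on assumed inputs, and that the 4.1 mm case uses the top of the SD range. At the middle of the ranges the rate at n = 56 is 33% rather than 42%.

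Finally, a Visit 2 value does not make within-group tests causal. Natural course, the dietary education given to all arms and the expectations of unblinded participants remain in them for every outcome. A Visit 2 value removes the part that is specific to this schedule.

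**Conclusion.** The point stands for the VAS. Its only pre-treatment value is the qualifying score from before the run-in, so the planned within-group tests will count regression to the mean and run-in change as improvement in every arm. Under the assumed ranges the spurious fall is about 0.9 to 6.5 mm. False improvement then appears in about 10% to 73% of tests at n = 56, against a nominal 2.5%. Run-in change is additional and cannot be sized from the documents. For HADS depression the artefact runs towards worsening, by at most about 1 point under the assumptions used. Between-arm results may lose some precision from the older baseline, but the documents do not allow that loss to be quantified. This should be corrected, but it does not threaten the trial's main conclusions.

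**What to change.** Collect the VAS and HADS at Visit 2, before the envelope is opened, and name those values as the baseline for both outcomes. Visit 2 already takes six other questionnaires from every participant, so the burden is a few minutes each. The change is a protocol modification, which under section 2.15 needs reapproval by the IRBs (three are listed) and an update of the registry entry.

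If that is not wanted, or if participants have already passed Visit 2, drop the within-group tests for VAS and HADS, or label them descriptive. State that conclusions on these outcomes come only from the between-arm comparison, with the screening value as a covariate. This adds no data collection. The cost is giving up the within-group p-values for two secondary outcomes. Neither option changes the sample size.
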